## Abstract

**Background:**

Family carers of older adults often experience significant mental health challenges, including anxiety and depression. Although online coaching interventions have been found to reduce anxiety and depressive symptoms in carers, only a few studies have examined the broader impact of applying online self-help interventions for enhancing resilience and overall well-being in carers. This study evaluates the effectiveness of a self-directed e-coaching intervention for family carers of older adults aimed at reducing anxiety and depressive symptoms, while also assessing its impact on enhancing their resilience and overall well-being, particularly for those with mild levels of carer needs.

**Objective:**

This study aims to evaluate the effectiveness of a self-directed e-coaching intervention in reducing symptoms of anxiety and depression among carers of older adults using the 7-Item Generalized Anxiety Disorder Scale (GAD-7) and 9-Item Patient Health Questionnaire (PHQ-9), respectively, and also to examine secondary outcomes to determine its broader impact, including improvement in the level of carer needs, quality of life, caregiving burden, self-care efficacy, and resilience.

**Methods:**

This is a 3-arm randomized controlled trial that involves family carers of older adults living in Hong Kong, who will be randomly assigned to one of the e-coaching intervention groups or the control group through an online platform. The e-coaching intervention will consist of structured modules for self-directed learning on lifestyle intervention, family relationships, and emotion regulation. Participants in the intervention groups will either receive full content or partial content tailored to their caregiving needs. A total of 240 participants will complete the GAD-7 and PHQ-9 assessments at baseline, postintervention, and at a 3-month follow-up to evaluate changes in anxiety and depression scores. Secondary outcome measures will include standardized measurements assessing the level of carer needs, quality of life, caregiving burden, self-care efficacy, and resilience. It is hypothesized that participants in both e-coaching intervention groups will demonstrate a statistically significant reduction in anxiety and depressive symptoms at both postintervention and 3-month follow-ups compared to the control group, in terms of reductions in GAD-7 and PHQ-9 scores.

**Results:**

This randomized trial was funded for an original project period from January 2023 to January 2028. The enrollment commenced in April 2025 and is ongoing, with the expectation of closing enrollment in May 2026. We anticipate that data analyses will be completed by September 2026.

**Conclusions:**

The anticipated findings from this study could provide valuable insights into the potential of e-coaching as an accessible self-help intervention for improving mental health outcomes among carers of older adults, particularly those classified with mild levels of carer needs. If successful, this self-directed approach may offer a scalable solution to alleviate psychological distress and enhance overall well-being and resilience in this vulnerable population. The results will inform future mental health strategies and interventions tailored for carers, ultimately fostering a healthier caregiving environment.

## Introduction

### Background 

Population aging is a ubiquitous global phenomenon, with an estimated one-sixth of the world’s population expected to be aged 60 years or more by 2030 [1]. Hong Kong has become a significantly aged society, with 23.3% of its population aged over 65 years [2] as of 2024, and it is experiencing rapid aging at an accelerating rate. It is projected that by 2046, the percentage of the population aged over 65 years will increase to 36% [3]. By 2050, the estimated percentage of the global aging population is projected to be just 22% [1]. Consequently, Hong Kong is trending toward having one of the oldest populations in the world. The societal challenges that arise from a super-aged society will be significant if not addressed promptly.

In light of Hong Kong’s transition to a super-aged society, the role of family carers has become increasingly vital. There are approximately 280,000 family carers of older adults in Hong Kong [4], which accounts for about 3.79% of the local population. This percentage is notably lower than those in several European countries, such as 13% in Spain and Portugal and 25% in Denmark and Belgium [5]. Traditional Chinese cultural values may help explain this discrepancy, as strong family ties often lead carers to not identify themselves as carers [6,7]. Consequently, this lack of recognition can result in many family carers embarking on their caring journey without formal training, which frequently leads to elevated stress levels and associated emotional symptoms [8-10]. As a result, the burden on family carers in Hong Kong is considerable. Therefore, providing support for these family carers is essential to maintain an effective caregiving ecosystem for older adults aging in place in Hong Kong [11]. For instance, an intervention designed for carers of dementia patients in the United States has been adopted and tested in Hong Kong, yielding favorable results that demonstrate its effectiveness [12].

Longitudinal studies have documented the negative impact of informal caregiving on the mental health of family carers, which deteriorates as they enter the caregiving journey and as care demands increase [13,14]. Additionally, decreases in leisure time and sleep time are thought to negatively affect carers’ subjective well-being [15]. A cross-sectional study by Lee et al [16] found that 28% of carers of patients with Parkinson disease were diagnosed with at least one psychiatric disorder, including depressive disorder (11.1%) and insomnia (6.4%). These rates are significantly higher than those observed in the general population (depression: 2%‐5%; insomnia: 4%) [17].

Various aspects and risk factors affecting carers’ mental health have been explored. Poor mental health has been linked to caregiving burden and challenges faced by carers of older adults. A study involving Chinese family carers of older adults in Shanghai revealed that carers’ competence had a significant impact on their quality of life and was mediated by the caregiving burden [18]. The researchers emphasized the importance of early identification and targeted measures, such as reducing caregiving burden, to mitigate potential health-related issues among family carers. Additionally, a group of researchers led by Ho et al [19] conducted in-depth interviews with Chinese-Canadian women who were carers for their spouses with Alzheimer disease. They reported feeling obligated to ensure their spouses’ well-being and regarded institutionalization as highly undesirable. Many expressed feelings of fatigue and an inability to relax psychologically.

In Hong Kong, Chow and Ho [11] investigated depression among older spousal carers and found that depression in this group was largely influenced by individual psychological resources, such as purpose in life, caregiver burden, and personal well-being. They urged the development of mental health programs aimed at enhancing these psychological resources for spousal carers. Given the high prevalence of psychological disturbances among carers and the need to bolster their individual psychological resources, there is a pressing need for evidence-based interventions and effective service delivery models specifically designed for carers.

### Interventions for Carers

#### Family Relationships

Family relationships have been reported as one of the stressors for carers of older adults [20-22]. Several empirical studies have investigated interventions aimed at positively influencing family relationships through communication skills training in various forms, including peer facilitation [23], home visits [24], and internet programs [25]. In particular, a study by Drossel et al [26] explored the effect of dialectical behavior therapy (DBT) skills training for family carers of people with dementia in a group setting. DBT focuses on helping individuals regulate their emotions, improve interpersonal effectiveness, develop distress tolerance, and practice mindfulness and has been studied for its efficacy in treating mood disorders, such as depression and anxiety [27-30]. The results suggested that DBT skills training improved carers’ problem-focused coping, enhanced emotional well-being, and reduced sense of fatigue, although the isolated effects of each individual skill were not reported in the study. Therefore, further exploration of the impact of interpersonal effectiveness on carers’ family relationships and psychological well-being is essential.

#### Lifestyle Intervention

In recent decades, researchers have shown a growing interest in the connection between lifestyle choices and mental health. When implemented effectively, improvements in lifestyle can serve as a low-cost, self-sustaining intervention to promote mental well-being. In New Zealand, White et al [31] followed the diets of 281 young adults over 21 consecutive days and showed that eating fruits and vegetables led to positive effects. They found that the benefits of eating fruits and vegetables not only improved mood on the day of consumption but also extended to the following day. Studies in the United States and Europe found a similar connection between healthy diet, physical activities, and mental well-being [32,33]. Regarding the prevention of mood disorders, supportive evidence for lifestyle interventions has also been found. In one systematic review, Mammen and Faulkner [34] analyzed the results from 30 longitudinal studies and found that physical activity was negatively associated with the risk of subsequent depression, and low levels of physical activity (<150 minutes of walking per week) were effective in preventing depression. A meta-analysis [35] of physical activity interventions found small-to-medium effects (*g*=0.37) on overall mental health (burden, depression, stress, and quality of life), with the most notable effect on quality of life (*g*=0.74). Carers of older adults often report high stress levels due to the demanding and continuous nature of their caregiving responsibilities. It has been suggested that lifestyle interventions focusing on better nutrition, daily exercise, and mind-body practices can effectively improve the ability to manage stress [36].

#### Low-Intensity Cognitive Behavioral Therapy

Given the high prevalence of psychological distress among carers, there is a strong need to develop evidence-based interventions to alleviate their psychological symptoms and support them in dealing with the demands of caregiving. In the literature, low-intensity cognitive behavioral therapy (LiCBT) has been a primary focus of studies concerning psychological interventions for carers [37-39]. LiCBT is an approach to disseminate CBT that aims to improve the accessibility of psychological treatment in the United Kingdom [40]. Unlike traditional CBT, which typically involves longer sessions led by trained clinical psychologists, LiCBT is delivered in 30-minute weekly sessions over a span of 6 to 8 weeks by mental health workers. To improve the efficiency and accessibility of LiCBT, self-help materials, computerized programs, and group delivery formats are often used.

A meta-analysis by Kaddour et al [38] analyzed studies of LiCBT in addressing anxiety, depression, subjective burden, and distress among carers of people with dementia. They found that LiCBT had a significant effect in reducing psychological difficulties experienced by carers compared to nonactive control groups. Small effect sizes were found for anxiety (*g*=0.35), depression (*g*=0.27), and distress (*g*=0.33). A medium effect was found for caregiving burden (*g*=0.53). A meta-analysis [41] on the effectiveness of clinician-guided and self-guided online cognitive behavioral therapy in reducing anxiety symptoms found that there was no significant difference for follow-up effect, with only a very small effect size at posttreatment (*g*=0.16). These studies suggest that an online-based self-guided LiCBT is a potentially effective, cost-effective, and accessible intervention to alleviate the psychological difficulties of carers in the community.

#### Self-Directed e-Coaching Intervention

The studies mentioned above highlight the need to promote mental well-being and alleviate psychological disturbances in carers, emphasizing the effectiveness of family relationships, lifestyle, and LiCBT interventions. However, attending therapy groups in person may not be feasible for carers of older adults due to limited mobility or the challenge of leaving older adults alone at home. Carers often face barriers such as a lack of transportation, the absence of a secondary carer, and inflexible schedules that hinder participation in demanding interventions [42]. Programs conducted in community settings typically have lower attendance rates compared to home-based options, such as telephone counseling and technology-based interventions [42].

In this context, internet-based interventions offer a convenient and cost-effective alternative [43-45]. Online educational programs provide flexibility for family carers, while e-coaching merges technology with personalized support for behavior change [46,47]. Our intervention focuses on individuals with lower psychological risk who are comfortable using computer and mobile devices for internet connection. A series of online self-help modules, developed by clinical psychologists of the research team, synthesizes three key areas: (1) lifestyle medicine, (2) LiCBT, and (3) interpersonal effectiveness. The goal of the e-coaching is to alleviate stress and prevent early psychological symptoms from progressing into serious illness, using a self-directed approach to enhance resilience and quality of life among carers.

### Objectives

This study aims to evaluate the effectiveness of a self-directed e-coaching intervention in reducing symptoms of anxiety and depression among carers of older adults using the 7-Item Generalized Anxiety Disorder Scale (GAD-7) and 9-Item Patient Health Questionnaire (PHQ-9), respectively, and also for secondary outcomes, including multidimensional needs assessment, resilience, quality of life, caregiving burden, and self-care efficacy.

### Hypotheses

It is hypothesized that participants in both intervention groups, either receiving full content or partial content tailored to their caregiving needs, will show a greater reduction in anxiety scores and depression scores, as measured by the GAD-7 and the PHQ-9, respectively, at both the postintervention and 3-month follow-ups compared to those in the control group. It is also hypothesized that participants in both intervention groups will experience improvements in secondary outcomes, including the multidimensional needs assessment, resilience, quality of life, caregiving burden, and self-care efficacy.

## Methods

### Study Design

This study is a 3-arm, single-blinded randomized controlled trial developed in accordance with the SPIRIT (Standard Protocol Items: Recommendations for Interventional Trials) checklist (Table 1). The research team will perform individual randomization using statistical software and assign the content through an e-platform to carers with mild needs. It will consist of a 6-week intervention period, with a screening process to be conducted prior to the intervention implementation. Statistical comparisons will be performed at baseline (T0), immediately postintervention (T1), and at a 3-month follow-up (T2) (Table 1). This study will be conducted from April 2025 to September 2026.

**Table 1. T1:** Schedule of enrollment, intervention, and assessments.

	Study period					
	Enrollment	Allocation	Postallocation			
Timepoint	*−t* _1_	0	Baseline	Treatment	Immediately postintervention	3 months postintervention
Enrollment						
Initial eligibility screen	✓					
Informed consent	✓					
Allocation		✓				
Interventions						
e-coaching 1				✓		
e-coaching 2				✓		
Control				✓		
Assessments						
JCCSP^a^ carer multidimensional need assessment	✓		✓		✓	✓
PHQ-9^b^			✓		✓	✓
GAD-7^c^			✓		✓	✓
EQ-5D-5L			✓		✓	✓
WHOQOL-BREF^d^			✓		✓	✓
ZBI-12^e^			✓		✓	✓
SCSES-10^f^			✓		✓	✓
CD-RISC-10^g^			✓		✓	✓

a JCCSP: Jockey Club Carer Space Project.

b PHQ-9: 9-Item Patient Health Questionnaire.

c GAD-7: 7-Item General Anxiety Disorder Questionnaire.

d WHOQOL-BREF: World Health Organization Quality of Life–BREF.

e ZBI-12: Zarit Burden Interview.

f SCSES-10: 10-Item Self-Care Self-Efficacy Scale.

g CD-RISC-10: 10-Item Conner-Davidson Resilience Scale.

### Ethical Considerations

The protocol for this study has been registered with ClinicalTrials.gov under the identifier NCT06604481 on September 18, 2024. The registration was completed prospectively before the enrollment of the first participant. We obtained ethical approval from the Human Research Ethics Committee at the University of Hong Kong (#EA240545). Informed consent will be obtained from all participants included in the study. To safeguard confidentiality, participant identities will be anonymized within the system. Withdrawal from the study is voluntary at any time and will not impact their access to other services offered by the project.

### Participant Recruitment

Potential participants will be recruited from 10 district-based carer support units and 8 shared venues operated by the 6 community partners. Recruitment will commence in April 2025. Given the challenges of identifying and engaging the target participants, a rolling recruitment strategy will be used until the group assignment is completed, which is anticipated to take 12 months. Carers will be recruited if they meet the inclusion criteria (Textbox 1), pass at least one threshold in the 2 specified parameters, and express a willingness to join.

Textbox 1.Inclusion and exclusion criteria.Inclusion criteriaBeing an adult aged 18 years or above with a family member aged 60 years or above requiring caregivingReporting a mild level of need in the Carer Multidimensional Need AssessmentProviding at least 6 hours of care per weekSelf-identifying as a family carerLiving in Hong KongAble to read ChineseVoluntary participationAble to use an electronic device independently
**Exclusion criteria**
Experiencing acute health conditions that hinder caregiving support or intervention participationHaving been diagnosed with Alzheimer disease or other types of dementia

The screening process involves carers completing a standardized form comprising demographics items and their willingness to participate. They can fill this out independently or with assistance from project staff upon enrolling. The research team developed a 22-Item Carer Multidimensional Need Assessment, which involves 5 domains of needs including physical health, mental health, social support, caregiving needs, and caregiving ability. Carers’ needs are categorized into 4 distinct levels: low, mild, moderate, and high [48].

### Sample Size Estimation

Sample size was calculated using analysis of covariance adjusting for baseline, and the longitudinal linear mixed model will be used as the primary analysis to use all repeated measures and available data.

According to a prior meta-analysis, internet-based self-help interventions for mental health demonstrate a medium effect size when compared to passive control conditions such as care-as-usual and waitlist [49]. According to another systematic review and meta-analysis of the effectiveness of internet-based psychoeducation programs for carers of people with dementia, internet-based psychoeducation programs had a significant impact on reducing carers’ depressive symptoms, with an effect size of −0.19 compared to control conditions [50].

Power analysis was conducted with G*Power 3.1.9.7. Assuming a medium effect size in the analysis of covariance, *α*=.05, power=0.80 [51], a total of 158 participants are required to join the study. Considering a possible attrition rate of 33%, the research team will set the minimum sample size at 240, with 80 participants in each arm [52].

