#### Control Group

On the other hand, the placebo-controlled group attends 6 weekly online sessions that primarily provide video-based educational information in a self-directed format on the same e-platform. The focus of the content will be on practical caregiving skills and promoting general well-being, rather than targeting any particular psychological or mental health–related factors directly. The control group will include all content listed in Table 4. The total duration of the control group lasts about 50 minutes. Control group adherence will be the number of videos completed by the participants. The control condition is designed as an “information-only” educational comparator, reflecting standard educational resources typically accessible to caregivers in the community. It does not include the interactive e-coaching component or structured home practice and does not overlap with the content provided in the intervention arm. This approach allows us to test the intervention materials and evaluate the added value of interactive e-coaching and guided self-help practice over standard educational materials.

**Table 4. T4:** Topics and content of control Group.

Topics	Content
Caregiving experience	Video regarding sharing of other carers’ experiences.
Introduction to knowledge of aging-related health issue and pain management	Videos of early detection of dementia and emotional problems. Videos address strategies for managing and alleviating chronic pain in older adults.
Caregiving resources	Videos of community support resources, including hotline, respite, equipment rental services, useful mobile apps, and support network of community centers.

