### Statistical Analysis

#### Primary Outcome Analysis

The linear mixed model will be used to evaluate the hypothesis regarding whether there is a reduction in anxiety and depression symptoms in the intervention groups compared to the control group. The model will include treatment conditions (e-coaching 1, e-coaching 2, and Control), assessment time points (baseline, immediately post intervention, and 3 months post intervention), and their interaction (group-by-time) effects as fixed effects. To account for the correlation of repeated measures within individuals, a random intercept for participants will be included. Anxiety and depression scores will serve as the dependent variables in separate models. Statistical significance is defined as alpha levels less than .05. Planned contrasts will separately compare each active intervention group (e-coaching 1 and e-coaching 2) against the control group at immediately post intervention and 3-month follow-up to evaluate intervention efficacy. Holm-Bonferroni correction will be applied to control the familywise error rate across multiple contrasts.

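### The stated 80% power at 158 participants belongs to a three-group omnibus F test, not to the Holm-adjusted contrasts that decide efficacy; at the planned 33% loss those have roughly 60–68% power on average

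*Protocol article*

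**What the plan says.** The Sample Size Estimation section gives the method ("Sample size was calculated using analysis of covariance adjusting for baseline"), the software ("Power analysis was conducted with G*Power 3.1.9.7") and the effect ("Assuming a medium effect size in the analysis of covariance"). Alpha is .05, undivided. The result is "power=0.80 [51], a total of 158 participants are required to join the study". The allowance for loss follows: "Considering a possible attrition rate of 33%, the research team will set the minimum sample size at 240, with 80 participants in each arm". The same section names a longitudinal linear mixed model as the primary analysis.

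The Primary Outcome Analysis section fits separate models for anxiety and depression. It bases efficacy on planned contrasts of each e-coaching arm against control, immediately after the intervention and at 3 months. It adds: "Holm-Bonferroni correction will be applied to control the familywise error rate across multiple contrasts". That makes 2 arms × 2 times = 4 contrasts per outcome, or 8 over both outcomes. The section does not say which of these counts is the Holm family. The Hypotheses section expects benefit in both active arms, on both scores, at both times.

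**The concern.** The sample-size section and the analysis section describe different tests. An omnibus F test asks whether three means differ anywhere. A Holm-adjusted contrast asks whether one named arm beats control, at a smaller alpha for all but the last step. Power computed for the first does not carry over to the second.

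What is at stake is interpretation. A reader who meets a non-significant contrast will weigh it against the published 80%. If the real power of that contrast was nearer 60–70%, a null result says less than the protocol leads the reader to believe. This is a conflict between two stated parts of the article, so it does not depend on anything an unseen analysis plan might add.

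**Working it through.** **Inputs.** From Sample Size Estimation: three arms, baseline covariate, medium effect, alpha .05, power 0.80, N = 158, 33% attrition, 240 enrolled at 80 per arm. From Primary Outcome Analysis: 4 contrasts per outcome, 2 outcomes, Holm. Assumed: medium means Cohen's f = 0.25, because the article gives no number.

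**1. Reproduce 158.** Noncentral F for ANCOVA with noncentrality λ = f²N, 3 groups, 1 covariate and denominator df = N − 4. The smallest N with power of at least 0.80 is:

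| Numerator df | Meaning | N |
|---|---|---|
| 1 | one contrast | 128 |
| 2 | three-group omnibus | 158 (power 0.802) |
| 4 | larger joint test | 196 |

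Only numerator df 2 matches, and it matches exactly. Attrition: 158/0.67 = 236, consistent with 240. In reverse, 240 × 0.67/3 = 53.6 per arm; 158/3 = 52.7 per arm is used below.

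**2. Convert f to a pairwise effect.** Let both active arms differ from control by d. The deviations from the grand mean are −2d/3, d/3 and d/3, so the variance of the means is 2d²/9 and f = d√2/3. Then d = 3 × 0.25/√2 = 0.53.

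**3. Power of one contrast.** Two-sided noncentral t, noncentrality d√(n/2) = 0.53 × √(52.7/2) = 2.72, error df 154:

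| d | .05 | .05/4 | .05/8 |
|---|---|---|---|
| 0.53 | 77% | 58% | 48% |
| 0.50 | 72% | 52% | 42% |

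The .05/4 and .05/8 columns are the first Holm step only. Later steps use a larger alpha, so these columns understate Holm.

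**4. Full Holm step-down.** Simulation with 200,000 draws of correlated z statistics, every contrast truly non-null. The correlation is 0.5 between arms, from the shared control. Correlations of 0.5 between times and between outcomes are assumed. Average power per contrast:

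| d | family of 4 | family of 8 |
|---|---|---|
| 0.53 | 68% | 60% |
| 0.50 | 62% | 53% |

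**5. Effect detectable with 80% power** at about 53 per arm: d ≈ 0.66 at .05/4 and 0.71 at .05/8.

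**6. How far the result moves.**
- No loss at all (80 per arm, d = 0.53): about 80% at .05/4. Step-down averages are 88% (family of 4) and 84% (family of 8).
- Equally spaced means with the same f = 0.25: the variance of the means is 2δ²/3, so δ = 0.25 × √1.5 = 0.306, and the two contrasts are d = 0.31 and 0.61. At 52.7 per arm with a family of 4, step-down power is about 27% for the weaker arm and 77% for the stronger.

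**The case against.** Nothing in the sample-size section is miscalculated: 158 and 240 both reproduce. The section also says openly that sizing used ANCOVA while the mixed model is primary. Neither f = 0.25 nor the omnibus test is written down; both are inferred from the exact match. That inference stands, but it is an inference.

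The 33% is described as possible attrition, and the plan uses all available data. Loss may come mostly after the first follow-up. If 66 per arm remained at that point (an assumption), step-down power there would be about 78% in a family of four, and with 70 about 81%. If medium meant d = 0.5 on the raw SD, a baseline correlation of 0.5 to 0.7 (also assumed) would raise power at .05/4 to 67–86%. The article places the effect inside the ANCOVA and claims no such credit, so this remains a possibility only.

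A reader might infer more than the documents support:
- *That every planned contrast is well short of 80%.* This depends on full loss at both times and on the pattern of arm effects.
- *That the trial needs all eight contrasts to succeed.* The hypotheses name both arms, outcomes and times, but no section makes that a success criterion, and the arms are compared separately. Power to find at least one contrast within an outcome is about 88% at d = 0.53.
- *That the Holm family must be eight.* Separate models make four per outcome a natural reading.
- *That the effect size itself is refuted.* The cited interventions "demonstrate a medium effect size when compared to passive control conditions such as care-as-usual and waitlist", whereas this control is an information-only programme "reflecting standard educational resources typically accessible to caregivers in the community", and the section also cites −0.19 for depressive symptoms in dementia carers. Whether a medium effect is plausible here is a separate question from which test the 80% describes.

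**Conclusion.** The point holds in this form: the 80% is a property of a test that the plan does not use to judge efficacy. Under the plan's own loss and its own medium effect, with both arms equally effective, average power per Holm-adjusted contrast is about 68% (four per outcome) or 60% (eight pooled), against a stated 80%. Even without any adjustment it is about 77%. The size rests on f = 0.25, equal arm effects, about 53 per arm at both follow-ups, and the assumed correlations in the simulation. With full retention the step-down shortfall disappears at d = 0.53.

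This is a mismatch between design and analysis, not an arithmetic error. Holm still controls the familywise error within whichever family is chosen, and the estimates and intervals are unaffected.

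**What to change.** Keep 240 participants and rewrite the power paragraph:

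1. Give the effect size as a number, and say that 158 evaluable participants provide 80% power for the three-group omnibus F test only, on one outcome at one time.
2. State the Holm family before analysis: four contrasts per outcome, or all eight. Either can be defended, but the power statement must match the choice.
3. Report for that family the average power per contrast at about 53 per arm (about 68% or 60% at d = 0.53; 62% or 53% at d = 0.50) and the detectable effect (d about 0.66 at .05/4, or about 0.71 at .05/8). Add the full-retention figure so that the dependence on attrition is visible.
4. State the assumed pattern of arm effects, since unequal effects move the two arms' power in opposite directions.

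The cost is a reworded paragraph and a less favourable stated power. No participants are added and the analysis model does not change, so it can be done while enrolment continues.
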